A complementary, inexpensive framework for malaria planning, monitoring and evaluation is offered by school malaria surveys (12-14). The practical advantages of sampling children at school are clear: identification and selection of individuals is simplified, compliance is high, and costs are reduced, since only a fraction of the population is examined. In addition, ministries of education are increasingly developing or upgrading national school databases using geographical information systems (GIS). This allows incorporation of information on school locations and enrolment into a single database, and the use of geo-statistical methods to model risks between schools and across un-sampled schools. There are also important epidemiological reasons for sampling children who attend school. Historically, malaria endemicity was defined on the basis of PR among children aged 2-10 years, and geographical reconnaissance of malaria was recommended in all areas prior to a control program launching into an attack phase of the Global Malaria Elimination Program (15). Recent mathematical models of malaria transmission dynamics indicate that EIR determines both the rate at which PR rises during early childhood and the age at which maximum PR is attained (16). Age-stratified studies in varying transmission settings reveal that PR consistency has a convex relationship with age, with PR rapidly rising among young children, attaining a maximum within the 5-10 year old age class, and declining among adolescents and young adults, thereafter maintaining a relatively stable low value throughout adulthood (17). Such consistency in the relationship between PR and age permits age-standardization of available PR estimates to the 2 to 10 year age range on the basis of catalytic conversion models (17), although estimates are most precise when the majority of the sampled population are within this age range.

The Uganda Malaria Surveillance Project (UMSP) is implementing routine surveillance of outpatient monthly malaria cases, laboratory confirmed suspected malaria cases, the prescription practices of health workers and anti-malarial drug usage at six sites across the country.

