### 5.3.2 Screening of participants

At the end of the household questionnaire, the study personnel will discuss the clinical survey aspect of the study with the head of the household or their designate and adult household members present. Study personnel will briefly describe the purpose of the clinical study in the appropriate language. The inclusion criteria are: 1) Usual residents who are present in the sampled households on the night before the survey, 2) children under 15 years of age or selected household members aged 15 years or older, 3) agreement of parents or guardians of children to provide informed consent, 4) agreement of eligible adults to provide informed consent and 5) agreement of a child aged 8 years or older to provide assent. The exclusion criterion is: 1) inability to locate the child on more than 3 occasions, 2) inability to locate other eligible respondents on more than 3 occasions. All children under 15 years of age will be included for the clinical survey. One person in each of the age category 15-24 years, 25-34 years, 35-44 years, 45-54 years, and > 55 years shall be randomly selected for the clinical survey.

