## 6.3. Initial recruitment and consent

Schools in the participating sub-counties will be selected using simple random sampling from a list of all primary schools in the sub-county generated during the enumeration exercise. Prior to the day of the survey, staff from participating schools will be sensitized about the study and plans for recruitment. A random sample of 150 children aged 6-15 years will be selected from each school using the school register. Thirty children will be randomly selected from each of the classes 2-6 in the selected schools to participate in the study. The parents/guardians of selected children will be invited to the school for a meeting with the study teams, to review the selection criteria for study participation and to gain informed consent. During the meetings, the purpose and procedures of the study will be discussed, informed consent forms will be distributed (appendix 6), and written informed consent will be sought from the parents/guardians. Those parents who do not attend the school meetings will be visited at home and the consent will be sought from their homes. Consent forms will be made available in the local languages and in English. Consent to take part in the research study (appendix 6) and consent for future use of biological specimens (appendix 7) will be sought. Details about the location of the students’ homes will also be obtained from the parent/guardians to facilitate tracing in the event the child is selected for household mapping.

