# STATISTICAL ISSUES

## 8.1 Outcome measures

| Outcome | Definition |
| --- | --- |
| Prevalence of anemia | Proportion of Hb measurements < 11.0 g/dL. Anemia will be classified according to severity: mild (Hb 8.0 – 10.9), moderate (Hb 5.0 – 7.9), severe (Hb < 5.0). |
| Parasite prevalence | Proportion of study participants with a positive thick blood smear at the time of assessment |
| IRS coverage | Proportion of households sprayed |
| ITN coverage. | - Percentage of household with at least one bednet  - Percentage of household with at least one ITN  - Average number of nets per household  - Average number of ITNs per household  - Percentage of children age who slept under any net the prior night  - Percentage of children age who slept under an ITN the prior night  - Percentage of pregnant women who slept under any net the prior night  - Percentage of pregnant women who slept under an ITN the prior night |
| IPT coverage | Percentage of pregnant women on intermittent antimalarial treatment or antimalarial chemoprophylaxis |
| ACT’s coverage | Proportion of febrile episodes in children treated with an ACT |
| Prompt effective treatment of fever | Proportion of children with fever treated within 24 hours of onset of symptoms with an ACT |
| Under five Crude Death Rate (all cause mortality) | The number of children who die by the age of five, per thousand live births. |
| Under five malaria mortality rate | Proportion of deaths in children under five attributed to malaria per thousand live births. |
| Prevalence of malaria specific immune responses | Proportion of study participants with malaria specific immune responses at the time of assessment  Antibody density in participants at the time of assessment |

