## 8.2 Analytical plan and sample size/power calculations

Statistical analysis will be undertaken using Stata 10 (Stata Corp., College Station, TX, USA). The prevalence of malaria infection will be based on the thin and thick blood smear readings. This procedure will enable estimation of parasite density, differentiation of Plasmodium species and identification of gametocytes. The proportion of children infected with single and multiple parasite species and the mean intensity of infection/parasite density will be calculated. Differences in proportions by age, sex and transmission setting will be assessed by logistic regression and differences in means using a Student t-test (for parametric data) and a Mann-Whitney test (for non-parametric data). Prevalence of infection and anemia, and coverage rates will be presented as frequencies with appropriate 95% binomial confidence intervals. The report and other related documents will be extensively disseminated to stakeholders. Avenues for dissemination will include publications, working papers, and atlases.

Infection. The primary metric used to measure infection for both the gold standard method (community surveys) and streamlined method (school surveys) will be the parasite rate (PR), defined as the number of positive blood smears divided by the number of smears examined. For the gold standard method, PR will be measured using the cross-sectional surveys of an estimated 300 children (200 households x 1.5 children per household) aged 6-14 years from the community surveys. For the streamlined method, PR will be estimated using cross-sectional surveys of 300 children (3 schools x 100 children per school) aged 6-14 years from the primary school surveys.

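### Parasite prevalence is fixed as a crude proportion although selection is unequal by design: a pooled community figure leans towards children, and the school-community difference may be distorted

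*Protocol*

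**What the plan says.** **Estimator.** Protocol 8.1 defines parasite prevalence as "Proportion of study participants with a positive thick blood smear at the time of assessment". Protocol 8.2 defines PR, the primary infection metric for both community and school surveys, as "defined as the number of positive blood smears divided by the number of smears examined". Prevalence of infection and anemia and "coverage rates will be presented as frequencies with appropriate 95% binomial confidence intervals". No weights are stated. Age standardisation is named only for antibody results (7.5).

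**School sample.** "Schools in the participating sub-counties will be selected using simple random sampling from a list of all primary schools in the sub-county" (6.3), three per site. "Thirty children will be randomly selected from each of the classes 2-6 in the selected schools to participate in the study" (6.3), and the first 20 eligible per class are enrolled, 100 per school (6.4), whatever the enrolment.

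**Community sample.** Households are drawn at random from an enumerated list, and those without a child of appropriate age are removed (5.1.1). Every child under 15 in a selected household is tested. For older members the rule is "One person in each of the age category 15-24 years", and likewise one in each of the four higher bands (5.3.2). The comparator for the school survey is "an estimated 300 children (200 households x 1.5 children per household) aged 6-14 years" (8.2).

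**Age pattern.** Section 1.3 describes PR as "attaining a maximum within the 5-10 year old age class, and declining among adolescents and young adults".

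**The concern.** A crude proportion estimates the population value only if everyone has the same chance of being sampled, or if the outcome is unrelated to that chance. Neither is assured here.

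- **Community prevalence (objective 1).** Children are taken in full and older members are subsampled. The protocol's own account of PR by age implies that pooling all participants pulls the figure towards the child rate.
- **School-community comparison (objective 2).** Pupils of small schools and small classes are over-represented, and equal quotas from classes 2-6 need not give the age mix of community children aged 6-14. Either feature could shift the difference between methods when PR at each age is the same in both, or could mask a real difference. That difference is judged against 10 points (8.2).

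**Working it through.** **1. The plan's own figure.** Inputs from 8.2: 300 children per method, one-sided 0.05, 10-point difference, PR 20-80%. Treating the samples as independent and equal-probability, without clustering:

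power = Φ(0.10 / √(2p(1−p)/300) − 1.645)

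At p = 0.50 the standard error is √(0.50/300) = 0.0408, and power = Φ(2.449 − 1.645) = 78.9%. At 40% or 60% it is 80.4%, and at 20% or 80% it is 92.2%. The stated 80% is reproduced to within about a point at the worst case, on the footing that no weights are needed.

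**2. Pooled community prevalence.** Table 1 gives 4.5 to 4.8 persons per household. Assumed: 2.4 children and 2.3 older members, a fraction f of older members tested, child PR a and older-member PR b.

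- True value = (2.4a + 2.3b) / 4.7
- Crude value = (2.4a + 2.3fb) / (2.4 + 2.3f)
- f = 0.9, a = 30%, b = 10%: true 20.2%, crude 20.7%, excess 0.5 points
- f = 0.8, a = 50%, b = 20%: true 35.3%, crude 37.0%, excess 1.7 points
- f = 0.6, a = 60%, b = 15%: true 38.0%, crude 43.6%, excess 5.6 points
- f = 1, or a = b: excess 0

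**3. School and class size.** With M schools in the sub-county, a pupil's selection probability is about (3/M) × (20 / enrolment of that class in that school). The correct relative weight is therefore the class enrolment, which the crude ratio sets to 1. The protocol gives no enrolments, so these are assumptions.

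- Schools of 300/600/900 with PR 60/50/40%: crude 50.0%; weighted (300×60 + 600×50 + 900×40)/1800 = 46.7%; shift +3.3 points.
- Across the scenarios tried, in which smaller schools have higher PR: +1.7 to +7.5 points. The shift is zero if PR is unrelated to size, and the sign reverses if larger schools have the higher PR.
- Class size, with larger lower classes and PR falling by class: −0.5 to −2.5 points.

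**4. Age mix, with the same PR at each age in both samples.**

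- Ages uniform over 6-14, PR 60/50/40% at 6-9/10-12/13-14: community 52.2%; school 56.0% if classes 2-6 hold ages 7-11 (+3.8), 51.7% if ages 8-13 (about −0.6).
- Steeper pattern 60/45/30%: community 48.3%; school 54.0% (+5.7) or 47.5% (−0.8).
- School sample 0.7 to 1.4 years older on average, PR falling 1 to 4 points per year: −0.7 to −5.5 points.

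The sign depends on the ages in classes 2-6, which the protocol does not give beyond the limits of 6 to under 15.

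**5. What a shift would do.** At PR 50%, an artefact of 2 points lowers power to show similarity to Φ(0.08/0.0408 − 1.645) = 62%; 4 points lowers it to 43%.

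**6. What weighting costs.** Kish design effect for three equal samples = 3Σw²/(Σw)². Sizes 300/600/900 give 3(9 + 36 + 81)/18² = 1.17, effective n 300/1.167 = 257. Sizes 200/500/1100 give 3(4 + 25 + 121)/18² = 1.39, effective n 216. With 300 on the community side, power at PR 50% is about 76% and 72%. Class-size weights alone give 1.02 to 1.13.

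**The case against.** Four points are fair and limit the finding.

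- **The household age bands do not touch the method comparison.** A reader might infer that they bias the school-community difference. That comparison uses ages 6-14 only, and the community side takes every such child in randomly drawn households, so it is self-weighting (reading a child of appropriate age in 5.1.1 as including ages 6-14).
- **Coverage is part of the method under test.** Leaving out class 1, class 7 and out-of-school children is a property of a school survey, so a gap that results is real disagreement. Standardising school PR to community ages borrows data that a stand-alone school survey would lack, and as the only comparison it could hide what objective 2 seeks.
- **The protocol plans for systematic bias.** Section 8.2 assesses differences by age, explores over- or underestimation whatever the test shows, adjusts by ecological regression and validates the models. The school method is rejected only if it fails to approximate the community result and correction is also unreliable.
- **Weights could be left to an analysis plan.**

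The first two points stand in full. The third stands in part. Ecological regression recalibrates survey-level estimates, of which 3 sites × 2 surveys × 2 years = 12 pairs are assured (4.1). It does not correct the crude PRs entering the direct test, nor the pooled community prevalence. Schools are also redrawn for each survey (6.1), so a size-related artefact need not be a constant offset. The fourth point carries less weight because 8.1 and 8.2 do not leave the estimator open; they state it as a crude ratio.

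**Conclusion.** The concern holds in two parts of unequal strength.

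1. **Pooled community prevalence, computed as written, overstates parasitemia.** The direction follows from the sampling rule and the age pattern in section 1.3. The size, about 0.5 to 6 points, rests on an assumed household split, fraction tested and PR by age. It is zero if all older members are tested or PR is flat across ages. A reader might take all-age prevalence to be a named primary outcome. It is not: it is implied by the 8.1 definition and objective 1, and the problem arises only if ages are pooled without weights. The documents give no age gradient for anemia across this range, so no direction is claimed there.
2. **The school-community difference may be distorted.** A reader might infer that it is biased. The documents do not support that: it requires PR to vary with school size, class size or the difference in age mix, and enrolments and age distributions are not given. The separate effects can offset, and the sign of the age effect changes between plausible cases.

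**What to change.** **In 8.1 and 8.2, community surveys.** Report parasitemia and anemia by age group. If a pooled figure is given, weight each tested person aged 15 or older by the number of eligible residents in that household age band, taken from the household questionnaire roster (5.1.4). State that the figure covers only households with a child of appropriate age (5.1.1).

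**In 8.2, school surveys.** Weight school PR by school and class enrolment from the registers already used for selection. Say that the weights are approximate, because the first 20 eligible of 30 selected per class are enrolled after consent and screening. Keep the comparison without age standardisation as the test of the school method. Add an age-adjusted comparison (by year of age, 6-14) to separate age mix from true disagreement. Replace simple binomial intervals with survey-based ones for weighted estimates.

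**Cost.** Wording and modest analysis time. Ages and the roster are already collected, and enrolment has to be recorded from the registers. Weighting loses some precision: illustrative design effect 1.17 to 1.39 from school size, with power at PR 50% falling from about 79% to 76-72%. For comparison, an uncorrected 2-point artefact would lower it to 62%.

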# 4.0 STUDY METHODS

## 4.1 Overall study design

We propose to conduct cross-sectional surveys in communities and primary schools twice a year for at least 2 years in the 3 different sites. The surveys will be timed to correspond to the high and low malaria transmission seasons, when possible. In the community surveys, 200 households will be recruited from a list randomly generated from a census database at each site. The community surveys will consist of three components: (1) a household survey targeting heads of households, (2) a women’s survey targeting all women of child-bearing age (15-49 years), and (3) clinical surveys of all children under fifteen years of age, and of one household member within the age category 15-24 years, 25-34 years, 35-44 years, 45-54 years, and > 55 years. The clinical surveys will include a fingerprick blood sample for measurement of hemoglobin, thick and thin blood smear, rapid diagnostic test (RDT) for malaria, and filter paper blood sample. The school surveys will be conducted in 3 randomly selected primary schools per site. A total of 100 randomly selected children will be recruited in each school. The school surveys will include only the clinical assessments including measurement of temperature, and a fingerprick blood sample for measurement of hemoglobin, thick and thin blood smear, RDT for malaria, and filter paper blood sample.

##

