## 5.1 Household survey

### 5.1.1 Selection of households

A sample of 200 residential households will be selected in each site. In order to create a sampling frame for the selection of participating households, all residential households within each of the three sites have been enumerated and mapped prior to the onset of the surveys as part of a separate protocol. A random sample of households will be selected from each site using computer-generated random numbers to generate a list of households to be approached. Study personnel will conduct door-to-door recruitment to identify those households with at least one adult household resident in sequential order according to the recruitment list. Households without a child of appropriate age will be removed from the recruitment list. Residents not home during the initial contact will be re-visited on at least three other occasions before eliminating them from our sample selection process. New recruitment lists will be randomly generated for each survey using replacement.

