## 6.0 SCHOOL SURVEYS

## **6.1 Overview.**

Surveys will be conducted in three schools per site which will be randomly selected from a list of all primary schools in the sub-county generated during an enumeration exercise which has already been completed as part of a separate protocol. The surveys will be done twice a year (once during the rainy season and once during the dry season). New lists of three schools will be randomly generated for each survey using replacement; as a result the same school may participate in the survey more than once.

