We will test the hypothesis that estimates of PR will be similar using the two methodologies. Point estimates of PR will be calculated for each biannual survey and compared using the McNemar’s test of paired proportions. Assuming that we will have a sample size of 300 children per survey for each methodology, we will have 80% power (one-sided significance level of 0.05) to reject the alternative hypothesis that there is a difference in estimates of PR assuming that the absolute difference in PR is no greater than 10% across a range of PRs in the community surveys of 20-80%. Whether or not these analyses show any evidence of significant differences between the methods, we will explore whether there is any systematic bias in the estimate of the streamlined method compared to the gold standard method (e.g. the streamlined method consistently over- or underestimates PR). Ecological logistic regression models will be used to predict the result of the gold standard method using data from the streamlined method, allowing adjustment for bias. Final models will then be prospectively validated in independent test sets to insure their accuracy.

Mortality. The primary metric for malaria mortality will be the relative change in absolute measures of malaria mortality. For the gold standard method, the measure of malaria morality will be the number of malaria-associated deaths in children under 5 years of age per 1,000 live births. Data on malaria mortality using the gold standard method will come from the biannual community surveys and verbal autopsy. For the streamlined method, the measure of malaria morality will be the number of malaria-associated deaths in children under 5 years of age captured by our inpatient surveillance system (described in another protocol).

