We will test the hypothesis that relative changes in malaria mortality will be similar using the two methodologies. Point estimates of relative mortality from one year to the next will be calculated and compared, by calculating the variance of the streamlined method using the delta method and the variance of the gold standard method using a bootstrap test. Assuming that we will have a sample size of 800 children per year from the community surveys with baseline mortality rates of 6.5, 12.9, and 19.4 per 1000 (based on 2006 Uganda DHS survey and assuming malaria-attributable mortality of 20%, 40%, and 60%), and baseline number of malaria-associated deaths from our inpatient surveillance of 12, 60, and 84 (based on preliminary inpatient surveillance data) for low, medium, and high transmission sites respectively, we will have 80% power (one-sided significance level of 0.05) to reject the alternative hypothesis that there is an absolute difference in estimates of relative mortality of 1.30, 0.50 and 0.41 for low, medium, and high transmission sites, respectively. Whether or not these analyses show any evidence of significant differences between the methods, we will explore whether there is any systematic bias in the estimate of the streamlined method compared to the gold standard method (e.g. the streamlined method consistently over- or underestimates relative mortality). Log-linear regression models will be used to predict the result of the gold standard method using data from the streamlined method, allowing adjustment for bias.

Immunology. The age-dependent SCR will be determined for each study area at each time-point and related to the concurrent parasite prevalence by RDT, microscopy and PCR and anemia prevalence.

Evidence for a change in transmission intensity will be assessed by fitting more than one force of infection to age-dependent antibody prevalence data. Antibody prevalence and density in school children will be related to the concurrent parasite prevalence by RDT, microscopy and PCR and anemia prevalence.

Decision on the optimal methods for surveillance. If any of the streamlined methods described above do not approximate the corresponding gold standard methods and attempts at correcting systematic bias are not reliable (e.g. unable to consistently predict estimates using the gold standard method) then we will conclude that the streamlined method is not a reasonable substitute for the gold standard method.

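### The 80% power for comparing school and community parasite rates covers one site in one survey, but the substitution conclusion rests on at least four such comparisons per site with no stated link

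*Protocol*

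**What the plan says.** Protocol 4.1 plans surveys "twice a year for at least 2 years in the 3 different sites". Section 8.2 (Infection) states a hypothesis of similar PR under the two methods. It applies the test survey by survey: "Point estimates of PR will be calculated for each biannual survey and compared". Power is given as 80% at a one-sided level of 0.05 for an absolute difference of 10 points, for community PR between 20% and 80%: "Assuming that we will have a sample size of 300 children per survey for each methodology".

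The sample sizes behind this are an "estimated 300 children (200 households x 1.5 children per household) aged 6-14 years" for the community method and "300 children (3 schools x 100 children per school) aged 6-14 years" for the school method. Section 5.1.1 sets the households by site ("A sample of 200 residential households will be selected in each site"), and section 6.1 does the same for schools ("Surveys will be conducted in three schools per site which will be randomly selected").

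Section 8.2 ends with a decision paragraph. Its first condition reads "If any of the streamlined methods described above do not approximate the corresponding gold standard methods". A second condition, joined by *and*, is that attempts to correct systematic bias are unreliable. If both hold, the streamlined method is judged not to be a reasonable substitute. Neither condition carries a number, and neither refers back to the per-survey tests.

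**The concern.** The protocol fixes a test, a significance level and a power for one unit (a site in a survey) and draws its conclusion on another unit (the method). Nothing connects the two. If three of four surveys at a site agree and one does not, the same data can be reported as agreement or as disagreement, and that choice stays open after the results are seen.

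Objective 2, the comparison of school with community estimates, feeds directly into this decision. The prevalence estimates themselves are unaffected. What lacks a pre-specified basis is the statement that schools can, or cannot, stand in for community surveys, and a reader who takes the 80% as the power for that statement will be misled.

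**Working it through.** **1. What the 300 is.** Community: 200 households × 1.5 children = 300. Schools: 3 × 100 = 300. Both 200 households and 3 schools are per-site numbers (sections 5.1.1 and 6.1), so 300 versus 300 is one site in one survey. Pooled over sites, a survey would give about 900 per method. That the comparison is made by site is inferred from this arithmetic; the Infection paragraph does not say so.

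**2. How many comparisons.** 2 surveys a year × at least 2 years = at least 4 per site; × 3 sites = at least 12. There is no upper limit, because the duration has none.

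**3. Reproducing the 80%.** Treat the two samples as independent proportions.

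- True difference zero, margin 10 points, one-sided 0.05, PR 50%: SE = √(2 × 0.5 × 0.5 / 300) = 0.0408. Power = Φ(0.10/0.0408 − 1.645) = 0.789. At PR 20% or 80% it is 0.922.
- Detecting a true 10-point difference, one-sided 0.05: lowest power 0.794 (40% versus 50%, or 50% versus 60%).

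The stated 80% is therefore reproduced within about one point, for one site in one survey. It covers one direction only. Showing similarity in both directions (two one-sided tests) at PR 50% gives 2 × 0.789 − 1 = 0.58.

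**4. What four comparisons at a site would do under two possible rules.** The protocol states neither rule. The correlation of 0.5 is an assumption (equicorrelated normal test statistics).

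| Rule | Independent | Correlation 0.5 |
|---|---|---|
| All 4 must show similarity, 80% each | 0.80⁴ = 41% | 56% |
| Any 1 significant difference counts, 0.05 each | 1 − 0.95⁴ = 19% | 14% one-sided, 16% two-sided |

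The first row takes the protocol's 80% at face value. The second row is the chance of at least one false difference when the methods truly agree.

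**5. What one pooled estimate per site would do.** Take the mean of 4 survey differences at PR 50%, with a 10-point margin and 5% on each side. The school ICC and a community design effect of 1.1 are assumptions. School design effect = 1 + 99 × ICC. Variance for one survey = (0.25/300) × (school design effect + 1.1); the mean of four has a quarter of that. Power = 2Φ(0.10/SE − 1.645) − 1, set to zero if negative.

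| School ICC | Design effect | SE, one survey | Power, one survey | SE, mean of 4 | Power, mean of 4 | All three sites |
|---|---|---|---|---|---|---|
| 0.02 | 2.98 | 0.0583 | 6% | 0.0292 | 93% | about 80% |
| 0.05 | 5.95 | 0.0767 | 0% | 0.0383 | 67% | about 30% |
| 0.10 | 10.9 | 0.1000 | 0% | 0.0500 | 28% | about 2% |

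The last column is the single-site power cubed, assuming independent sites all at PR 50%. With independent children and no design effects, the mean of four gives 99.9% and one survey 58%.

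These are normal approximations. With only 12 school draws per site over four surveys, and schools that can be drawn again, true power would be somewhat lower.

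**The case against.** The strongest reply is that nothing is misstated. The protocol openly gives its power per survey, the figure reproduces, and nowhere does it claim that this power governs the final conclusion. Multiplicity methods are commonly left to the SAP, which is not shown. This largely stands, and the absence of an alpha split or hierarchy is not held against the protocol. What remains is that the protocol itself fixes both per-survey testing and the closing decision, and leaves them unconnected.

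Second, the decision paragraph needs two conditions. A chance significant result cannot reject schools unless bias correction also proves unreliable. Section 8.2 also says that bias will be explored whatever the tests show, and that prediction models will be validated in independent data. This stands. It does not define what counts as approximating the gold standard, however, and it gives no protection against calling the methods similar too readily.

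Third, a reader might compute 1 − 0.95¹² = 46% and call it the error rate of the study's conclusion, or 0.80¹² = 7% and call it its power. The documents do not support either. No rule says that any one of 12 tests decides, or that all 12 must pass. Failing the first condition is not enough to reject schools, and the objectives are framed by epidemiological setting, so a site-by-site reading with four surveys is at least as natural.

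Fourth, averaging over surveys blurs the high- and low-season contrast built into section 4.1. That is a real cost, and it is the reason to keep the per-survey results in the report.

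**Conclusion.** The point holds as a gap between the quoted power and the conclusion, not as an error in the power figure. The 80% is sound for one site in one survey if children are treated as independent. It does not describe a conclusion built on at least 4 surveys per site. How far it misses depends on the unstated rule: 41% to 56% if all four must show similarity, or a 14-19% chance of at least one false difference if any one counts. Both ranges are illustrations that rest on an assumed correlation between 0 and 0.5, and the second is not the probability of wrongly rejecting schools.

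The case for change is that a better and inexpensive method exists on data already planned. At PR 50% with an assumed school ICC of 0.02, equivalence power rises from about 6% for one survey to 93% for the mean of four. The gain shrinks quickly as the ICC rises, and the protocol gives no ICC, so this should be checked before anything is promised. This is a worthwhile improvement rather than a fatal flaw.

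**What to change.** In section 8.2 (or in the SAP, with a cross-reference):

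- Name one deciding estimate per site: the mean school-minus-community PR difference over the surveys of the first two years. Take it from one model with survey as a stratum and a variance that allows for schools and households.
- Define the first condition of the decision paragraph by whether the 90% confidence interval of that estimate lies within the protocol's own ±10 points, and state the conclusion site by site.
- If one overall conclusion requiring all three sites is wanted, say so and give its power. At PR 50% this is about 80%, 30% or 2% at assumed school ICCs of 0.02, 0.05 or 0.10, against 93%, 67% or 28% for one site.
- State that the existing 80% is a per-site, per-survey figure.
- Report the per-survey differences alongside, as checks of seasonal consistency.

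The cost is a change of wording and one model on data already to be collected. The rule itself needs no added participants, but at the higher assumed ICCs the planned sample may not be enough to show similarity, and the restated power should say so. The main downside is that a mean can hide differences that change sign with season, so the per-survey differences must be shown next to it.
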